#### Reporting of Expedited Safety Reports

A suspected unexpected serious adverse reaction (SUSAR) is an SAE that occurs in a participant, the nature or severity of which is not expected per the applicable product information (ie, the investigator’s brochure).

The sponsor and investigator will report any SUSARs concerning the drug that has occurred in the study to regulatory authorities:

If it is neither fatal nor life-threatening, within 15 days after becoming aware of the information.If it is fatal or life-threatening, within 7 days after becoming aware of the information. The sponsor and investigator shall, within 8 days after having informed the REB and Health Canada of a fatal or life-threatening SUSAR, submit a complete follow-up report in respect of that information that includes an assessment of the importance and implication of any findings made.

### Statistics

#### Sample Size Determination

The sample size for this clinical investigation was calculated based on the results from the pilot study and the change from baseline to week 8 of the first 13 participants for the MADRS (primary endpoint) and GAD-7 scores (first secondary endpoint). The change from baseline to week 8 was used for the two endpoints, mirroring the time frame for the evaluation of the primary and first secondary endpoints for this clinical investigation. Two series of estimates were generated: change from baseline for the participants with scores at baseline and week 8, and a second imputed data set for participants who did not have a week 8 value using the last observation carried forward. Although the final analysis from this study will use multiple imputation to address missing data, using the last recorded observation results in a higher SD and is considered a reasonable approach to derive a range of estimates. Estimates from the pilot investigation are presented in Table S4 in Multimedia Appendix 1.

For estimation purposes, it is assumed that the placebo participants will have a response that is 50% of the active treatment group, and the SD will be the same between the two treatment groups. The randomization will be in a 1:1 ratio (active:placebo), and the type 1 error rate will be 5%. The resulting sample sizes for 80%, 85%, and 90% power are presented in Table S5 in Multimedia Appendix 1.

If the true mean difference between the active and placebo groups is the midpoint between the observed and imputed results, a minimum target sample size of 50 participants will be required for the primary endpoint (MADRS: change at 8 weeks) and 79 participants (GAD-7: change at 8 weeks) for the other endpoints. On the basis of these estimates, the maximum number of participants to be enrolled in this clinical investigation is 80, and the target sample size is 60 participants. An interim assessment will be performed after 30 participants have completed the 8-week evaluation or withdrawn prematurely.

#### Populations for Analyses

##### Intent-to-Treat Population

This population includes all participants who consent to participate, meet the inclusion criteria, and are randomized. All baseline characteristics will be summarized based on intent-to-treat (ITT). Participants in the ITT population will be analyzed according to the original treatment assignment, regardless of the actual treatment received. All baseline tables will be based on the ITT population. The ITT population will be the primary population for efficacy endpoints.

##### Per-Protocol Population

The per-protocol population is a subset of the safety population. It includes all participants who meet all of the following criteria:

No major deviations from protocol eligibility criteria;≥85% of compliance with the treatment schedule; and≥85% of compliance with all study visits where the samples will be obtained and the testing will be performed.

The per-protocol population will be used for the sensitivity analyses of the efficacy endpoints.

##### Safety Population

The safety analysis population will contain all participants who receive at least one dose of study medication (active or placebo). All safety tables will be based on the safety population.

### Statistical Analysis

The statistical analysis plan will be finalized before database lock and will include a more technical and detailed description of the statistical analyses described in this section. This section summarizes the planned endpoints and statistical analyses. Participants who return after the initial treatment but later withdraw from the study will have their final scores for primary outcomes projected to week 8. If data are missing, the data from the last time point will be projected forward.

Changes from baseline to endpoint in scores on the MADRS, HAM-A, CGI, SHAPS, QIDS-SR16, GAD-7, and Pittsburgh Sleep Quality Index will be analyzed using two-tailed *t* tests or analysis of variance between and within the placebo and active arms. All statistical tests will be performed using the statistical program IBM SPSS with a significance level of .05. Similarly, stool samples will be analyzed for their diversity scores using a paired *t* test and repeated measures analysis of variance. Any changes in diversity scores will then be compared with the clinical scores to determine any correlations.

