### Setting

This study will occur at 3 sites: the Providence Care Hospital, Kingston, Ontario, Canada; the Centre for Addiction and Mental Health, Toronto, Ontario, Canada; and the University of Minnesota Medical School, Minneapolis, Minnesota, United States. There will be a total of 6 visits: a screening visit, a baseline visit (week 0), 3 treatment-period visits (weeks 2, 4, and 6), and a 2-week follow-up visit as outlined in the schedule of assessments (Table S1 in Multimedia Appendix 1).

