### Efficacy Endpoints

#### Primary Efficacy Endpoint

At the first endpoint, we will assess changes in symptoms of depression from baseline to week 6 as measured by MADRS scores.

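### Free improvement: the comparison of MADRS change does not adjust for baseline MADRS, which the trial already collects; the planned test is valid but avoidably imprecise

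*Protocol article*

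**What the plan says.** The Statistical Analysis section of the protocol article lists "Changes from baseline to endpoint in scores on the MADRS, HAM-A, CGI, SHAPS, QIDS-SR16, GAD-7" and a sleep index, and says that these changes "will be analyzed using two-tailed *t* tests or analysis of variance between and within the placebo and active arms". It names no covariate, and no other section mentions ANCOVA, a mixed model or a baseline term. The Primary Efficacy Endpoint section fixes the time point: "we will assess changes in symptoms of depression from baseline to week 6 as measured by MADRS scores".

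The Study Design section puts 30 patients in each arm, and the Setting section says "This study will occur at 3 sites". MADRS is scored at baseline and at weeks 2, 4 and 6 (Secondary Endpoints). The Statistical Analysis section describes the SAP as a fuller technical account of the analyses named there, to be final before database lock.

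**The concern.** A change score subtracts the whole baseline value, which amounts to fixing the coefficient of baseline at 1. If the true slope of the final score on baseline is below 1, change remains correlated with baseline. This has two consequences in a trial of 60:

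- When the arms differ at baseline by chance, part of that difference stays in the estimated treatment effect.
- The error variance is larger than it need be, so power is lower and the confidence interval wider than the same data would allow.

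At stake is efficiency, and how well the estimate from the one trial actually run can be trusted. The validity of the test is not at stake.

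**Working it through.** **Inputs from the article.** 30 per arm (Study Design); two-sided 0.05 (Statistical Analysis); at least 50 patients for the MADRS endpoint, based on week-8 change (Sample Size Determination).

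**Inputs not available.** The pilot mean and SD are in Table S4, which is not shown, so 50 cannot be reproduced forward. The text does not say which power row gives 50: "The resulting sample sizes for 80%, 85%, and 90% power are presented in Table S5 in Multimedia Appendix 1". The baseline and final SDs and their correlation rho are not given. They are assumed below and varied.

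**Step 1: back-solve the effect.** With 25 per arm and 80% power, d = (1.960 + 0.842) × √(2/25) = 0.79 change SDs by the normal approximation, or 0.809 with the noncentral t. At 30 per arm, d = 0.809 gives 86.9% power for the planned t test. If 50 is the 85% or 90% row, d is 0.865 or 0.936, and power at 30 per arm is already 90.9% or 94.6%.

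**Step 2: chance imbalance.** The standard error of the baseline difference is √(2/30) = 0.258 baseline SD.

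**Step 3: formulas.** Let s0 and s1 be the baseline and final SDs.

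- Variance of change: s0² + s1² − 2·rho·s0·s1
- ANCOVA residual variance: s1²(1 − rho²)
- Slope of final score on baseline: rho·s1/s0
- Shift from a 1-SE imbalance: (1 − slope) × 0.258 × s0
- Effect in points: 0.809 × SD of change
- ANCOVA power: noncentral t with d/√ratio and 57 error degrees of freedom, where ratio is ANCOVA variance over change variance

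**Worked row (s0 = 7, s1 = 9, rho = 0.3).** Change variance = 49 + 81 − 37.8 = 92.2. ANCOVA variance = 81 × 0.91 = 73.71. Ratio = 0.80. Slope = 0.3 × 9/7 = 0.386. Shift = 0.614 × 0.258 × 7 = 1.11 points. Effect = 0.809 × √92.2 = 7.77 points, so the shift is 14% of it.

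**Results** (80% row assumed; only the ratio s0/s1 matters, and 5/9 to 7/9 stands for roughly 55–80%):

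| s0 / s1 | rho | Var change | Var ANCOVA | Ratio | Shift, % of effect | Power at N = 60 |
|---|---|---|---|---|---|---|
| 5 / 9 | 0.3 | 79.00 | 73.71 | 0.93 | 8 | 89% |
| 5 / 9 | 0.5 | 61.00 | 60.75 | 1.00 | 2 | 87% |
| 7 / 9 | 0.3 | 92.20 | 73.71 | 0.80 | 14 | 93% |
| 7 / 9 | 0.5 | 67.00 | 60.75 | 0.91 | 10 | 90% |
| 9 / 9 | 0.3 | 113.40 | 73.71 | 0.65 | 19 | 97% |
| 9 / 9 | 0.5 | 81.00 | 60.75 | 0.75 | 16 | 94% |
| 9 / 9 | 0.7 | 48.60 | 41.31 | 0.85 | 12 | 92% |

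Using d = 0.79 instead moves the shift ranges by at most one percentage point (2–15% and 13–19%).

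**Step 4: simulation check.** This used 20,000 trials per rho, 30 per arm, equal SDs and an effect of 0.79 change SDs. Power went from 86% to 96% (rho 0.3), 85% to 93% (0.5) and 86% to 90% (0.7). The change-score estimate moved with the imbalance at slopes of −0.69, −0.50 and −0.31, which match −(1 − rho); for ANCOVA the slopes were about 0. Mean bias of both estimators was within 0.003, so the imbalance is a conditional problem and not an average one.

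**The case against.** The strongest objection is that this is a condensed article with an unseen SAP, that covariates are often settled there, and that analysis of variance can loosely include covariate-adjusted models. This is fair but not decisive. The article does not leave the method open: it names one and says that the SAP will detail the analyses so named. An adjusted reading needs words that are not in the text.

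The objection on size largely stands. The equal-SD figures may be optimistic, because entry requires a MADRS of at least 15 and that may narrow the baseline spread. In the least favourable row the gain vanishes.

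A reader might infer several stronger points that the document does not support:

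- **That the entry floor makes the problem worse.** Truncating baseline weakens its correlation with change. In a simulation with the floor at the baseline mean and rho 0.3, the correlation went from −0.59 to −0.40. The floor is also stated for the screening visit, which is separate from baseline.
- **That a baseline imbalance passes in full into the effect.** Only the fraction (1 − slope) does.
- **That offering a t test or ANOVA leaves two rival primary tests.** With two arms, one-way ANOVA on change is the pooled t test (F = t²), and so is the group-by-time test with two time points.
- **That a site term is needed.** No site variance is given and the article does not describe stratification, so its benefit cannot be quantified.

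**Conclusion.** The point holds as a free improvement, not as an error. The planned comparison is valid, and a reader should not infer that it is biased on average or that its type I error is inflated. What it leaves behind is conditional bias in the realized trial and some lost precision.

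With a restricted baseline SD (rho 0.3–0.5), adjustment cuts variance by about 0–20%, and a 1-SE imbalance shifts the planned estimate by about 2–14% of the back-solved effect. With equal SDs (rho 0.3–0.7), the cut is 15–35% and the shift about 12–19%. Power at 60 patients rises from 87% to 87–93% or 92–97%.

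The direction is secure, but the size is not. It rests on assumed SDs and rho, on 50 patients being the 80% row (the gain is smaller for the 85% or 90% row), and on an effect from a week-8 calculation applied to a week-6 endpoint.

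**What to change.** In the Statistical Analysis section, replace the sentence on t tests or ANOVA with one prespecified primary between-arm model, and carry it into the SAP before database lock. Either of these would serve:

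- ANCOVA on week-6 MADRS with treatment and baseline MADRS; or
- a repeated-measures mixed model on MADRS at weeks 2, 4 and 6 with treatment and baseline MADRS, allowing both to vary by visit, with the week-6 contrast as primary.

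Report the adjusted active-minus-placebo difference with its 95% CI. A site term is optional.

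The cost is one paragraph. Both models can be fitted in SPSS, the named software, and no new data are needed. In the ANCOVA, baseline takes one degree of freedom, and a three-level site factor would take two more. Even if adjustment brought no variance reduction (ratio 1.00), losing all three would move power only from 86.9% to 86.8%.

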**Methods:**

In this study, we will recruit 60 adults aged between 18 and 45 years old with major depression and randomly assign them to treatment or placebo groups. Patients in the treatment group will receive MET-2 once a day for 6 weeks, whereas patients in the placebo group will receive a matching placebo for 6 weeks. Participants will complete biweekly visits during the treatment period and a follow-up visit at 2 weeks post treatment. As a primary outcome measure, participants’ mood will be assessed using the Montgomery-Asberg Depression Rating Scale. Secondary outcome measures include changes in mood, anxiety, early stress, gastrointestinal symptoms, and tolerability of MET-2 treatment using a series of clinical scales and changes in blood markers, particularly immunoglobulins (Igs; IgA, IgG, and IgM) and inflammatory markers (C-reactive protein, tumor necrosis factor-α, transforming growth factor-β, interleukin-6, and interleukin-10). Changes in the relative abundance, diversity, and level of engraftment in fecal samples will be assessed using 16S rRNA sequencing. All data will be integrated to identify biomarkers that could indicate disease state or predict improvement in depressive symptoms in response to MET-2 treatment.

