## Methods

### Study Design

This study is a phase 2, randomized, double-blinded, placebo-controlled clinical trial exploring the efficacy of MET‑2 as a treatment for depressive symptoms in participants with MDD. We will randomize 60 participants with MDD into two arms: the treatment arm (30/60, 50%) and the placebo arm (30/60, 50%). Participants will consume either the investigational product MET-2 or a matching placebo daily for 6 weeks.

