## Results

This study was approved by the Queen’s University Health Sciences and Affiliated Teaching Hospitals REB on September 2, 2020. Owing to COVID-19–related delays, participant recruitment did not start until March 2021. Given the association between the GBA and symptoms of depression, it is expected that participants who receive MET-2 will have a significant reduction in depressive symptoms as determined by the MADRS compared with participants who received the placebo. This will be assessed by comparing pre- and posttreatment scores.

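### Within-arm tests stand beside the between-arm test at the same .05 level with neither named as decisive, and stool diversity is given a paired test with no arm contrast

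*Protocol article*

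**What the plan says.** The Study Design section describes the trial in these words: "This study is a phase 2, randomized, double-blinded, placebo-controlled clinical trial". The aim at the end of the Introduction is framed against placebo, and the sample size is built on an active-placebo difference.

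The Statistical Analysis section then covers change from baseline on seven scales (MADRS, HAM-A, CGI, SHAPS, QIDS-SR16, GAD-7 and the Pittsburgh Sleep Quality Index). They are to be analysed by two-sided *t* tests or "analysis of variance between and within the placebo and active arms". One level covers all tests: "IBM SPSS with a significance level of .05".

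In the Results section, the sentence that expects a greater MADRS reduction than on placebo is followed by: "This will be assessed by comparing pre- and posttreatment scores".

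For the microbiome, the plan says that "stool samples will be analyzed for their diversity scores using a paired" *t* test, together with repeated measures ANOVA. No comparison between arms is named in that sentence. It continues: "Any changes in diversity scores will then be compared with the clinical scores to determine any correlations". Whether arm enters that correlation is not said.

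**The concern.** Only a comparison of randomized arms isolates the effect of MET-2. A pre/post test inside one arm also picks up placebo response, regression to the mean after selection on a minimum MADRS score, and the passage of time. The plan gives such tests the same level as the between-arm test and does not label them descriptive. A significant improvement within the MET-2 arm could therefore be reported as a planned efficacy result even if the two arms did not differ.

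For stool diversity, which belongs to a declared secondary endpoint, the gap is wider. The paired test uses each person as their own control and makes no use of the randomization.

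The correlation between diversity change and clinical scores has a related weakness. If both arms are put into one correlation without an arm term, an effect of MET-2 on each variable separately creates an association even when the two are unrelated within each arm.

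**Working it through.** **Inputs.** From Sample Size Determination: a minimum of 50 participants in total for MADRS and 79 for GAD-7; 1:1 allocation; 5% type 1 error; placebo change assumed to be half the active change; common SD. From Study Design: 30 per arm. The pilot means and SDs and the table of N by power are in an appendix that is not shown. So N=50 cannot be reproduced forward, and the text does not say which of 80%, 85% or 90% power it belongs to. All three are carried below. The sizing figures refer to change to week 8; I assume that the same standardized change applies to the pre/post tests.

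**Step 1: standardized between-arm difference implied by N=50.** With n=25 per arm, the normal formula is d = (z₀.₉₇₅ + z_power)·√(2/n). At 80% power this is (1.960 + 0.842)·√(2/25) = 0.792. Solving with the noncentral *t* gives 0.809.

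**Step 2: placebo arm's own change.** If the active arm changes by A, placebo changes by A/2 and the difference is A − A/2 = A/2. The placebo arm's mean change therefore equals d.

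**Step 3: power of a pre/post test in the placebo arm alone.** This is a one-sample *t* test with n=30, 29 df and noncentrality d·√30. At 80% power the noncentrality is 0.809 × 5.477 = 4.43.

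| N=50 is the figure for | d (normal) | d (*t*) | Placebo pre/post test significant, n=30 | Between-arm power at 30 per arm |
|---|---|---|---|---|
| 80% power | 0.792 | 0.809 | 0.990 | 0.869 |
| 85% power | 0.848 | 0.865 | 0.996 | 0.909 |
| 90% power | 0.917 | 0.936 | 0.999 | 0.946 |

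With 25 evaluable placebo participants and d = 0.809, the probability is 0.972. For GAD-7 (N=79, d from 0.64 to 0.74) the placebo test at n=30 is significant with probability 0.92 to 0.97. If the true placebo change were smaller than the plan assumes, the MADRS figure would fall: 0.75 at 0.5 SD and 0.36 at 0.3 SD.

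**Step 4: MET-2 no better than placebo.** Both arms change by 0.81 SD, with 30 per arm and 20,000 simulated trials. The within-arm test in the MET-2 arm is significant in 98.9% of trials. The between-arm test is significant in 4.8%, which agrees with its nominal 5%.

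**Step 5: correlation, if arms are pooled.** Let MET-2 shift diversity by dx and mood by dy (in within-arm SDs), with no association within either arm. With equal arms, r = (dx·dy/4) / √[(1 + dx²/4)(1 + dy²/4)]. The documents give no value for dx, so it is an assumed range.

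| dx (assumed) | dy | r | Significant at .05, N=60 | Method |
|---|---|---|---|---|
| 0.5 | 0.81 | 0.09 | 11% | simulation |
| 0.81 | 0.81 | 0.14 | 19% | simulation |
| 1.0 | 0.8 | 0.2/√(1.25 × 1.16) = 0.17 | 24% | Fisher z |
| 1.2 | 0.81 | 0.19 | 32% | simulation |
| 1.5 | 0.8 | 0.3/√(1.5625 × 1.16) = 0.22 | 40% | Fisher z |

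**The case against.** A reader might infer that pre/post tests are the plan's evidence on mood. The text does not support that. The between-arm test is listed, and listed first. The aim, the hypothesis in the Abstract and the sample size are all set against placebo, and the intent-to-treat population is analysed by assigned arm. The Results sentence on pre- and posttreatment scores follows one that names the placebo comparison, so it can mean change scores compared between arms. This objection stands: for mood, the defect is only that no contrast is made decisive.

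For stool diversity, the sentence opens by likening itself to the one on the scales, and repeated measures ANOVA can carry an arm-by-time term. That is fair for the ANOVA. It does not rescue the paired test, which is a stated choice and cannot compare arms.

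Pooling of the correlation is an inference, since the handling of arm is unstated. Step 5 is therefore conditional.

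Two further readings should be set aside. No pre/post test of immune markers is stated anywhere, only a relationship with symptom improvement. The Abstract's hope to "identify biomarkers that could indicate disease state or predict improvement in depressive symptoms in response to MET-2 treatment" might suggest that the trial cannot address disease state because all participants have MDD. But that phrase may mean severity or remission, and it is an aspiration with no test attached. Models for predictors, including marker-by-treatment terms, may properly be left to the SAP.

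Finally, the 99% is the power to detect a real placebo change, not an error rate, and the plan also tests within the placebo arm, so that change would be visible. Both points are true. Seeing it is still no test of the difference between arms. Nor does the coming SAP settle the matter, because the section says that the SAP will describe these same analyses in more detail.

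**Conclusion.** The point holds in a limited form. The plan lists within-arm and between-arm tests of seven scales at one level without saying which decides efficacy, and it names a paired test for stool diversity without an arm contrast. The within-arm tests say almost nothing about MET-2. On the plan's own placebo assumption, the placebo arm alone would show a significant MADRS improvement with probability 0.990, or 0.996 or 0.999 if N=50 is the 85% or 90% power figure. These values rest on the 50% placebo assumption, a common SD and 30 evaluable participants. A smaller placebo change lowers the probability but does not make the test a comparison with placebo.

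If the diversity-symptom correlation ignores arm, it would be significant in about 10–40% of trials instead of 5%. That assumes arm shifts of 0.5–1.5 SD on diversity and about 0.8 SD on mood, with no within-arm association. The documents do not establish that the correlation will be pooled.

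The conclusion does not extend to a claim that the trial lacks a placebo-controlled test of mood, and it does not touch the sample size.

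**What to change.** 1. State in the protocol and the SAP that efficacy on MADRS and every other scale is judged only by the active-minus-placebo difference in change from baseline, preferably by ANCOVA with the baseline score as covariate. This also settles the open choice between *t* test and ANOVA.
2. Report within-arm changes as estimates with confidence intervals, labelled descriptive. Reword the Results sentence so that it refers to the difference between arms in change.
3. For stool diversity, replace the paired *t* test with a baseline-adjusted between-arm comparison, or with the arm-by-time term of the repeated measures model.
4. Include arm in the model for the association between diversity change and clinical scores, or report the association by arm.

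The same data serve all four changes and the sample size is unaffected. With 30 per arm, the between-arm MADRS test has about 87% power if N=50 is the 80% figure. The cost is that fewer results will be nominally significant.
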